### Interim analyses {21b}

No interim analysis is planned.

### Methods for additional analyses (e.g. subgroup analyses) {20b}

Similar statistical models as detailed for the primary and secondary outcomes above will be applied but include interaction terms between the treatment variable and the variables defining the subgroups. Specifically, differences in outcomes (between the two treatment arms) will be investigated for the following subgroups:Pathogen-specific subgroups (bacterial, viral, combined bacterial and viral group and those with unknown aetiology individually)Radiologically confirmed CAP and clinically suspected CAPPatients with severe versus non-severe pneumonia, based on different scoring systemsSputum samples judged as representative versus those judged as not representative by microscopic criteriaHospital ward allocationPatients with chronic pulmonary disease (chronic obstructive pulmonary disease, asthma, bronchiectasis) versus those withoutUse of antibiotics: on admission, within the preceding month prior to admission, within 48 h prior to admission

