### Intervention description {11a}

The trial evaluates the utility of diagnostic tests used for diagnosing the microbiological aetiology in CAP. Blood tests and cultures, urine sample for urine antigen tests, chest x-ray and samples from the respiratory tract are collected in all patients following inclusion. Due to local infection control measures, the patients’ SARS-CoV-2 status needs to be clarified before collecting samples from the lower respiratory tract. Following consent, all patients are tested for their SARS-CoV-2 status. A confirmed case of SARS-CoV-2 is defined as a positive result on the rapid XpertXpress SARS-CoV-2 or SARS-CoV-2/FLU/RSV test run on the GeneXpert system (Cepheid, Sunnyvale, U.A.) or on Cobas SARS- CoV-2 & Influenza A/B test run by the Cobas Liat System (Roche Molecular Systems, Inc., Pleasanton, CA) using naso-/oropharyngeal swab samples. Lower respiratory tract samples are collected after sputum induction or by endotracheal aspiration in both arms. On receipt of the lower respiratory tract sample at the Department of Microbiology, the patients are randomised to the following arms:

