#### *The FAP* plus *arm*

The FAP *plus* arm entails extended and rapid diagnostics on lower respiratory tract samples and telephonic feedback to treating staff with results. The feedback does not involve advice on treatment. All patients will receive the standard microbiological tests described above, with additional testing by the FAP *plus*. Through a feedback loop, both negative and positive FAP *plus* results are telephonically communicated to the treating staff.

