#### Secondary outcomes

There are 13 binary outcomes (encoded as yes/no):

Treatment with narrow-spectrum antibiotics within 48 h from study inclusionTreatment with a single dose of antibiotics onlyTreatment with antibiotics for not more than 48 h (within the first 7 days after inclusion)Treatment with intravenous antibiotics (within the first 7 days after inclusion)De-escalation from broad-spectrum to narrow-spectrum antibiotics (within the first 7 days after inclusion)Escalation from narrow-spectrum to broad-spectrum antibiotics (within the first 7 days after inclusion)Detected aetiology of CAP (within the first 7 days after inclusion)Provision of neuraminidase inhibitors to patients with diagnosed influenza (within the first 7 days after inclusion)Readmission within 30 days after dischargeDeath within 30 days, 90 days, 1 year and 5 years

There are eight quantitative outcomes:Duration of antibiotic use; intravenous and per-oral (in days)Duration of intravenous antibiotics (in days)Duration of broad-spectrum antibiotics (in days)Time from admission to time of pathogen-directed treatment (in hours)Time from admission to time of administration of antibiotic(s) (in hours)Time to appropriate use of isolation facilities (in days)Length of hospital stay (in days)Time from admission to a microbiological sputum test report (FAP *plus* result and/or sputum culture) (in hours)

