### Sample size {14}

To ensure a sufficiently large sample size to address the multiplicity issue introduced by considering two primary outcomes, we take a slightly conservative approach of assuming that the two outcomes are uncorrelated, implying that separate sample size calculations for the two outcomes must be carried out at a significance level of 0.025 instead of 0.05.

In a prospective study on hospitalized CAP patients, with stringent inclusion criteria (that included the presence of a new pulmonary infiltrate on chest radiograph), we showed that microbial aetiology with a combination of molecular and conventional methods could be established in 63% of included patients [22]. Therefore, for the proportion of patients with change in treatment from empirical antimicrobials to pathogen-guided treatment, we expect to be able to identify a pathogen in at least 50% of the cases using FAP *plus* versus 40% with the current standard-of-care methods.

The required sample size needed is 470 per arm (assuming a significance level of 0.025 and a power of 0.8), i.e., in total 940. Additionally, allowing for a 10% dropout rate results in a total sample size of 1045 patients. For the time to change from empirical treatment to pathogen-directed treatment, we have no data from previous studies on effect size to gauge the sample size calculation and therefore we will define the effect size in terms of the variation in the outcome (the standard deviation) as done in other studies [23].

We find it clinically relevant to be able to detect a difference of 0.2 standard deviations, e.g., if the standard deviation of the time to change is 3 days, then we can detect a difference of 0.2‧3 = 0.6 day; if the standard deviation was 5 days, we would detect a difference of 1 day. The required sample size needed is 477 per arm (assuming a significance level of 0.025 and a power of 0.8), i.e., in total 954. Additionally, allowing for a 10% dropout rate results in a total sample size of 1060 patients.

In conclusion, a sample size of 1060 will ensure that we have 80% power to detect a difference in at least one of the two primary outcomes (at a significance level of 0.05).

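### The aetiology subgroups are formed after randomisation from testing that differs by arm, so the arms within them are not comparable

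*Protocol article*

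**What the plan says.** All references are to the Protocol article.

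- **Subgroup analyses {20b}.** The models used for the main outcomes will "include interaction terms between the treatment variable and the variables defining the subgroups", and arm differences will be examined by subgroup. The first item listed is "Pathogen-specific subgroups (bacterial, viral, combined bacterial and viral group and those with unknown aetiology individually".
- **Timing, Intervention description {11a}.** "On receipt of the lower respiratory tract sample at the Department of Microbiology, the patients are randomised to the following arms". Allocation therefore precedes any result from the lower respiratory sample.
- **Testing by arm, the FAP plus arm.** "All patients will receive the standard microbiological tests described above", and FAP plus is added in that arm only.
- **Expected yield, Sample size {14}.** The investigators expect to "identify a pathogen in at least 50% of the cases using FAP *plus* versus 40% with the current standard-of-care methods".
- **Aetiology as an outcome, Secondary outcomes.** The list includes "Detected aetiology of CAP (within the first 7 days after inclusion".
- **Classification, Plans for assessment and collection of outcomes {18a}.** Two physicians independently judge the clinical importance of every microbiological finding, and a third settles disagreements. FAP plus results are not set aside. Section {17a} says that outcome assessors are not blinded.

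**The concern.** A subgroup comparison is protected by randomisation only if the subgroup would be the same whichever arm the patient was allocated to. Here the same patient can be unknown under standard testing and bacterial or viral under FAP plus. A patient classed as viral by the swab PCR can also move to the combined group when the panel adds a bacterium.

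The protocol cannot both expect the intervention to change detected aetiology and use it as a stratifying factor. Conditioning on it compares different kinds of patient in the two arms. The interaction term then mixes any real difference in effect with reclassification.

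At stake are statements such as a benefit in patients with viral or unknown aetiology, which readers would want to apply in practice.

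**Working it through.** **1. Reproduce the plan's figure.** The 50% and 40% come from the sample-size section, with significance level 0.025 (two-sided) and power 0.80.

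n per arm = [z(0.9875)·√(2·0.45·0.55) + z(0.80)·√(0.5·0.5 + 0.4·0.6)]² / 0.10²
= [2.2414·0.7036 + 0.8416·0.7]² / 0.01 ≈ 469.2, rounded up to 470.

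940 / 0.9 = 1044.4, rounded up to 1045. Both agree with the protocol, so 50% versus 40% is the planning assumption actually used.

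**2. Subgroup sizes.** The final sample of 1060 at 1:1 gives 530 per arm.

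| | Known | Unknown |
|---|---|---|
| Standard of care | 0.40 × 530 = 212 | 0.60 × 530 = 318 |
| FAP plus | 0.50 × 530 = 265 | 0.50 × 530 = 265 |

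**3. Reclassification.** Assume that FAP plus adds detections and loses none, in line with its add-on design. Patients then fall into three types: detected under either strategy (40%), detected only with FAP plus (10%, or 53 per arm) and never detected (50%).

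- Standard-arm unknowns who would be known under FAP plus: 53/318 = 1/6.
- FAP plus knowns who would be unknown under standard testing: 53/265 = 1/5.

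**4. False difference with no treatment effect.** Let a, f and u be the outcome rates in the three types, identical in both arms. The difference, FAP plus minus standard, is:

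- known group: (0.4a + 0.1f)/0.5 − a = 0.2(f − a)
- unknown group: u − (0.1f + 0.5u)/0.6 = (u − f)/6

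The document gives no values for a, f or u. All rates below are assumptions.

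| a / f / u (%) | Known (points) | Unknown (points) |
|---|---|---|
| 60 / 30 / 20 | −6.0 | −1.7 |
| 60 / 20 / 20 | −8.0 | 0.0 |
| 60 / 10 / 20 | −10.0 | +1.7 |
| 60 / 40 / 20 | −4.0 | −3.3 |
| 30 / 10 / 20 | −4.0 | +1.7 |
| 50 / 50 / 10 | 0.0 | −6.7 |
| 50 / 20 / 10 | −6.0 | −1.7 |
| not set / 20 / 50 | not computed | +5.0 |

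The known group shows −10 to 0 points and the unknown group about −7 to +5. By the formula, the known-group difference would turn positive if f exceeded a, a case not among these sets. The split into bacterial, viral and combined cannot be quantified, because no rates are given for it.

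**5. Influenza outcome, for comparison.** Let s be the share of FAP plus arm influenza cases found by the panel alone, and d the gap in treatment rates between those cases and the others. The false difference has size s × d. With s from 0 to 20% and d from 30 to 50 points (both assumed), it runs from 0 to 0.20 × 50 = 10 points. It is zero if the PCR shared by both arms finds the same cases.

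**The case against.** **The definition may be arm-neutral elsewhere.** Section {20b} does not say which tests assign aetiology. Every patient has the standard tests, and the full protocol and any SAP are not shown. A classification from standard tests alone would be compatible with the text. That is fair, but the article does commit to comparing arms within these groups, and the one classification process it describes uses all findings. Followed as written, it yields non-comparable groups.

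**The 50% and 40% are planning values.** They were set for the first primary outcome, not for seven-day detected aetiology. This stands: the 1 in 6 and 1 in 5 are indicative only.

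**These are additional analyses.** This also stands. Section {20c} analyses both primary outcomes on all randomised patients, and nothing here touches those estimates.

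**Ignoring FAP plus discards information.** True. Respiratory samples are frozen in the biobank, so running the panel on stored standard-arm samples, subject to consent, could classify both arms alike. It would cost more than a derived variable.

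**Stronger readings that a reader might infer.** Hospital ward allocation is also listed as a subgroup, and one outcome is "Provision of neuraminidase inhibitors to patients with diagnosed influenza". It is tempting to call both biased in the same way, but the document does not support that. It does not say when ward is recorded or that FAP plus changes it; the nearest text concerns isolation facilities. For influenza, both arms have the swab PCR, some of the permitted rapid tests run before lower respiratory sampling also cover influenza, and the article does not name influenza among the panel's targets. Bias is possible in both places but not shown, and for influenza it may be small or nil.

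**Conclusion.** The point holds for the aetiology subgroups. They rest on a post-randomisation classification that the plan itself expects to differ by arm and also counts as an outcome. On 50% versus 40%, and if FAP plus only adds detections, about one sixth of the standard-arm unknown group and one fifth of the FAP plus known group would change class under the other strategy.

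The resulting bias cannot be sized from the document. Under the assumed rates its sign changes in the unknown group, and it can be zero in either group, so no single row of the table should be read as the size of the problem. A reader might also infer that the trial's main result is compromised; it is not. Severity: should-fix for the additional analyses.

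**What to change.** State in {20b} that bacterial, viral, combined and unknown aetiology are defined identically in both arms. Use only the protocol-mandated standard tests that every patient receives (sputum and blood culture, swab PCR, pneumococcal urine antigen). Ignore FAP plus results and physician-requested tests; the latter can be prompted by a phoned result.

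The cost is wording and one derived variable from data already collected. The downside is that fewer patients are classed as having a known aetiology, and the extra FAP plus detections are not used for subgrouping.

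Two optional clarifications, where bias is possible but not shown:

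- use the ward assigned before the FAP plus result, or label that subgroup descriptive;
- define diagnosed influenza by the swab PCR or rapid test shared by both arms.

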### Methods in analysis to handle protocol non-adherence and any statistical methods to handle missing data {20c}

As CAPNOR is a pragmatic trial, the main statistical analyses will be carried out according to the intention-to-treat principle using appropriate effectiveness estimands [40]. Specifically, for the two primary outcomes, which are based on an event time, possibly subject to right censoring, the statistical analysis will be based on all patients that were randomised. Likewise, for event-time-derived secondary outcomes, statistical analyses will also be based on the full set of randomised patients. For other outcomes, where missing values may occur, missing values will be imputed using outcome-specific imputation models unless complete-case or available-case analyses could be justified because the missing data mechanisms are missing completely at random or missing at random, respectively.

### Plans to give access to the full protocol, participant-level data and statistical code {31c}

The full protocol and scripts used for the statistical analysis will be available on request once results of the study have been published. Patient-level data will not be available.

## Oversight and monitoring

### Composition of the coordinating centre and trial steering committee {5d}

The principal investigator (PI) will be scientifically responsible and responsible for communication internally within the consortium and with the main funder (Research Council of Norway). This includes compiling and submission of progress reports and financial reports. The PI will be supported by the core project management group (comprising senior CAPNOR group members based at the University of Bergen (UiB) and HUH), who will conduct regular meetings to monitor trial progress. In addition, advice will be sought on a case-to-case basis from the project’s independent scientific advisory committee. Responsibility for the data management and the contact person for questions regarding the use of research data lie with the project’s PI. The project’s data management team include three bioengineers (HUH), local Viedoc support designee, study nurses (three based at HUH), study doctors (four based at HUH/UIB) and a post-doctoral scientist (based at UIB).

### Composition of the data monitoring committee, its role and reporting structure {21a}

The study was reviewed by the sponsor and felt to be of low risk on the grounds that it is not a clinical trial of a medical treatment requiring active involvement or participation by patients. Therefore, the likelihood of harms associated with the interventions was judged to be low (see also {22} below), waiving the need for a data monitoring committee.

### Adverse event reporting and harms {22}

The FAP *plus* has demonstrated excellent sensitivity and specificity in multicentre evaluations [35, 36], and we consider the risks associated with this test to be low. Respiratory samples collected on admission are recommended as part of the standard of care, and our intervention therefore causes no additional risk. The risk of blood sampling in the form of pain, bleeding and infection is minimal. No other adverse events are anticipated, moreover, and no adverse effects were reported in our feasibility study [19]. However, monitoring and reporting of adverse events and severe adverse events will take place throughout the trial period. Any suspicion of trial-related adverse events will immediately be discussed in the CAPNOR study group, documented in our eCRF and reported, if applicable, in the trial publication. Treatment recommendations to escalate, de-escalate or stop antibiotic treatment may be beneficial for the individual patient by minimizing exposure to antibiotics and/or improving pathogen-specific targeted use of antibiotics. Final decisions will always be made by the treating physician taking into account all clinical and diagnostic information.

### Frequency and plans for auditing trial conduct {23}

Regular monitoring will be performed according to ICH GCP (International Conference on Harmonisation-Good Clinical Practice) by the sponsor, who will verify that the clinical trial is conducted in compliance with the protocol, GCP and applicable regulatory requirements.

### Plans for communicating important protocol amendments to relevant parties (e.g. trial participants, ethical committees) {25}

Amendments made to the study protocol after having obtained initial ethical approval will be (1) submitted to the REC for approval, (2) communicated to the funding agencies and (3) communicated in the main publications of the results of the CAPNOR trial.

### Dissemination plans {31a}

The results of this study will be published and presented at scientific meetings. The investigators will comply with the requirements for publication of study results. Authorship linked to publications ensuing from the trial will be determined based on substantive intellectual contributions. All contributions credited as authors will take responsibility and be accountable for what is published. Authorships will be based on the International Committee of Medical Journal Editors criteria. Currently, we have no plans of using professional writers. In addition, technical bulletins on methodological updates will be disseminated to appropriate partners. These publications will be restricted to the consortium unless agreed otherwise by all involved partners (for example, to make press releases). Importantly, we will publish the results of the proposed study in peer-reviewed international journals and relevant data will be made available in appropriate databases. Partners who identify a legitimate commercial interest may request a delay of no more than 60 days to allow for filing of patents, in which case the rules for protection of intellectual property rights, which will be laid out in the consortium agreement, will be followed. The standard rules on data protection will be followed, in which premature release of data is discouraged. However, on completion of data analysis and study closure, publication in the peer-reviewed literature will follow without unnecessary delays.

## Discussion

The COVID-19 pandemic spread to Norway during March 2020 and forced us to adapt to new routines and infection control measures deployed at hospitals and in the society at large. The planned start of the trial was therefore delayed with about 6 months. The time available to collect data and complete inclusions at the emergency department was initially restricted due to shortage of isolation facilities and a large inflow of patients. Initially, each patient is screened for SARS-CoV-2 before an induced sputum sample can be collected at the emergency department, with the subsequent risk of delaying the lower respiratory tract sampling. This is minimized by rapidly sending an oro- or nasopharyngeal swab for analysis by a rapid SARS-CoV-2 test, which provides results within 1 h.

With the national infection control measures, including social distancing, use of facemasks and home office solutions, the number of hospital admissions for lower respiratory tract infections at Bergen Health Trust fell during the first year of the pandemic [24]. This has resulted in slower inclusion rates than anticipated. Finally, COVID-19 and related quarantine among study staff has led to problems with optimal recruitment and timely pursuit of pre-defined study milestones due to absenteeism.

## Trial status

Protocol version 3; 21 August 2020. On September 25, 2020, the first patient was enrolled. As of February 2022, 354 patients have been enrolled. Recruitment of patients is ongoing and expected to be completed in May 2023. The investigators may initiate study-site closure at any time, provided there is reasonable cause and sufficient notice is given in advance of the intended termination. Reasons for the early stopping may include, but are not limited to, demonstrated efficacy, futility or inadequate recruitment of participants by the investigators. If the study is prematurely terminated, the investigators will promptly inform the REC and the contract research organizations of the reason for termination.

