### Assignment of interventions: blinding

### Who will be blinded {17a}

CAP patients are blinded for the intervention, and medical staff in the emergency department are blinded at patient inclusion and hence have no influence on allocation which is assigned at the Department of Microbiology, HUH. Owing to the nature of the intervention, research staff and clinical care providers are not blinded to group allocation. Furthermore, data managers, outcome assessors and statisticians are not blinded. However, in contrast to data managers and outcome assessors, the involved statisticians do not have any direct access to data, which are stored within the Viedoc platform for patient registry at HUH.

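### The protocol plans no interim analysis yet lists demonstrated efficacy and futility as reasons to stop early, so the 5% level is unprotected if the efficacy option is used

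*Protocol article*

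**What the plan says.** Five places in the protocol article bear on this.

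- **Interim analyses {21b}** consists of one statement: "No interim analysis is planned".
- **Trial status** lets the investigators start closure of the site at any time, given reasonable cause and notice. It continues: "Reasons for the early stopping may include, but are not limited to, demonstrated efficacy, futility or inadequate recruitment of participants by the investigators". The list is open-ended, and the next sentence speaks of premature termination of the study.
- **Composition of the data monitoring committee {21a}** judges the trial to be low risk, "waiving the need for a data monitoring committee".
- **Who will be blinded {17a}** says that "data managers, outcome assessors and statisticians are not blinded". It then adds a safeguard: unlike data managers and outcome assessors, the statisticians have no direct access to the data.
- **Sample size {14}** says that the calculations for the two primary outcomes "must be carried out at a significance level of 0.025 instead of 0.05", and concludes with 80% power at an overall level of 0.05.

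**The concern.** Whether efficacy has been demonstrated, or the trial is futile, is ordinarily judged by comparing the arms on the outcomes collected so far. Such a comparison is an interim analysis, whatever it is called. One section therefore says that none is planned, while another names two stopping reasons that would normally need one. Both are current text.

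An unseen analysis plan could not settle this quietly, because a stopping boundary written there would contradict the interim analysis section.

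What is at stake is the type I error. The two primary outcomes at 0.025 each use up the 0.05, and nothing is left for an earlier look. A stop on an unadjusted efficacy comparison would carry a higher error rate than stated and would tend to exaggerate the effect. A trial that closed short for purely logistical reasons would also be harder to defend, because its own protocol allowed a data-driven stop.

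**Working it through.** **1. Inputs from the protocol article**

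- Sample size {14}: 0.025 per outcome, 0.05 overall, power 0.8. Outcome 1: "at least 50% of the cases using FAP *plus* versus 40% with the current standard-of-care methods". Outcome 2: "We find it clinically relevant to be able to detect a difference of 0.2 standard deviations". The stated sizes are 470 and 477 per arm, and 1060 in total after 10% dropout.
- Interim analyses {21b}: none.
- Trial status: 354 patients enrolled by February 2022.

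**2. The plan's own figures**

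Two-sided 0.025 gives a critical value of 2.2414; power 0.8 gives 0.8416.

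- Outcome 1, n per arm = [2.2414·√(2·0.45·0.55) + 0.8416·√(0.5·0.5 + 0.4·0.6)]² / 0.1² = 469.2, rounded up to 470 (stated: 470).
- Outcome 2, n per arm = 2·(2.2414 + 0.8416)² / 0.2² = 475.3, rounded up to 476 (stated: 477, a difference of one).
- Dropout: 2·477 / 0.9 = 1060 (stated: 1060).

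The design reproduces as one final analysis, two-sided at 0.025 per outcome. The overall error is at most 0.025 + 0.025 = 0.05, or 1 − 0.975² = 0.0494 if the outcomes are independent.

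**3. Error rate if the trial can stop for efficacy at the unadjusted 0.025**

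The protocol gives no number or timing of looks and no correlation between the test statistics, apart from its conservative assumption that the outcomes are uncorrelated. Everything varied here is therefore an assumption.

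Under the null hypothesis, the z-statistics for one outcome at information fractions t1 < t2 have correlation √(t1/t2). Error per outcome = 1 − P(|Z| ≤ 2.2414 at every look). With uncorrelated outcomes, family-wise error = 1 − (1 − error per outcome)². For correlated outcomes it comes from simulated null trials, at least 1,000,000 per scenario.

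| Assumed looks before the final analysis | Per outcome | Family-wise, correlation 0 | 0.8 | 0.985 |
|---|---|---|---|---|
| None | 2.5% | 4.9% | 4.0% | 2.9% |
| One, at half the patients | 4.3% | 8.4% | 6.8% | 5.0% |
| One, at 354/1060 (33%) | 4.5% | 8.9% | 7.2% | 5.3% |
| Two, at thirds | 5.6% | 10.9% | 8.8% | 6.6% |

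Check of the uncorrelated column: 1 − (1 − 0.0428)² = 0.084, and 1 − (1 − 0.0562)² = 0.109.

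**4. Futility**

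Stopping for futility removes some trials that might later have rejected the null hypothesis. It adds no opportunity to reject, so it cannot raise the type I error; it can only lower power. The table applies to the efficacy reason alone.

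**The case against.** The strongest reply is that the interim analysis section is the operative statistical statement, and that the sample size is built for one final analysis. The stopping sentence sits under Trial status, next to site closure and contract research organizations, in a single-centre trial. It reads like general closure wording. If nobody looks, the 5% level holds. This stands, and it is why the point concerns reconciling the text.

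Some further points also stand:

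- The statisticians have no direct data access, so they should not be counted with those who could readily compare the arms. Outcome assessors are described as judging individual patients; no running comparison by arm is described.
- External evidence could conceivably bear on efficacy or futility, so an internal look is the ordinary route rather than the only one.
- At a correlation of 0.985, one look at half the patients leaves the overall error at about 5.0%, so not every scenario breaches the overall level.

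What the reply does not remove is the conflict. Closing the only site ends the trial, and the passage itself refers to early stopping. The text names efficacy and futility expressly and provides neither a boundary nor an independent committee.

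A reader might infer that the error rate is already inflated, or that slow recruitment points to a data-driven stop. The documents support neither. They report no look at the data by arm. Slower inclusion than anticipated makes a logistical stop more likely, which raises no error-rate issue if it is decided without outcome data by arm. Nor is it right that nobody would learn the reason for a stop: the protocol requires the ethics committee to be told why the study was terminated.

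**Conclusion.** The point holds as a should-fix contradiction. The protocol plans no interim analysis but permits early stopping for efficacy or futility, without a boundary or a monitoring committee, while data managers and outcome assessors are unblinded and have data access.

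The error rate is unprotected; it has not been shown to be inflated. The breach depends on the efficacy option being used at the unadjusted level, and its size depends on looks and correlations that the protocol does not give. Under the protocol's own working assumption of uncorrelated outcomes, the overall error would be about 8.4% with one look at half the patients and 10.9% with two looks at thirds. At a correlation of 0.985 these fall to about 5.0% and 6.6%. The futility reason bears on power only.

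**What to change.** Reconcile the two sections in one of two ways.

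- **If no efficacy or futility stopping is intended:** delete those two reasons from Trial status. State that closure for recruitment, funding or other logistical reasons is decided without outcome data by arm. Limit this restriction to logistical decisions, so that it does not hinder review of a safety concern; deaths and readmissions are themselves trial outcomes. The cost is a few words.
- **If such stopping is wanted:** replace the interim analysis statement with the number and timing of looks, a group-sequential boundary that keeps the overall 0.05 across both primary outcomes, a futility rule if one is intended, and review by people independent of the trial team. This costs a protocol amendment, a modest check of the sample size and the setting up of that review.

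Either change should be made before any decision to close early. If the trial does close early, the report should say whether anyone had seen outcome data by arm when the decision was taken.
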